#### Secondary outcomes

##### 1. Related to the primary outcome

*1.1 Volume effects*

The volume of referrals will be measured by the percentage of randomised participants over the study period who are referred by Lead Clinicians to secondary care, and compared between randomised groups as a difference in proportions with 95% confidence interval for the difference, and using the chi-squared test.

*1.2 Sensitivity, specificity and negative predictive value of the decision not to refer*

Sensitivity, specificity and other study proportions of lesions will be analysed using the same approach as for the primary outcome measure. These data will be used to compare the PPV of a referral (the primary outcome), and the NPV (correct management of lesions not referred) which will provide important data around lesions which are incorrectly identified as not suspicious in general practice. These data can contribute to further development of the diagnostic algorithm embedded in the MoleMate system.

##### 2. Clinical outcomes

Histological diagnosis of melanoma will be summarised as a rate in each randomised group, with the denominator being the participants in each randomised group: exact methods (95% confidence interval and Fishers exact test) will be used to estimate the difference in rates of melanoma. Melanoma thickness (Breslow data) and other histological diagnoses will be summarised using the same approach.

From five-year Cancer Registry follow-up for all participants (incidence and mortality) survival analysis methods will be used, including the log rank test, Kaplan Meier survival plots, and Cox regression to estimate intervention effects with 95% confidence intervals and associated p-value (involving the full participant sample in each randomised group (referred plus non-referred) to assess overall effect of the introduction of the MoleMate system compared to current best practice).

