#### 2.7.1 Referred lesions

All lesions considered 'suspicious' by a Lead Clinician from both trial arms are referred to secondary care (Addenbrooke's Hospital) via the normal two-week skin cancer care pathway, where one of three dermatologists (Experts A, B and C) provide an opinion as to whether or not the pigmented lesion is 'clinically significant'.

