##### Clinical outcomes

- Thickness of melanomas biopsied in secondary care clinics;

- 5 year melanoma incidence and mortality among trial participants collected through the Eastern Cancer Registration and Information Centre (ECRIC).

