The measures and interventions for the MoleMate UK Trial have been developed using the approach defined by the MRC Framework for development of complex interventions for evaluation in randomised trials [27,28] to ensure rigour, transparency and reproducibility. The four-month pilot phase confirmed the proposed recruitment and referral rates and the feasibility of participant randomisation. It demonstrated the feasibility of tracking referred participants in secondary care, and established mechanisms for reference standard diagnosis for all lesions recruited into the trial. During the pilot phase semi-structured interviews and questionnaires confirmed that both participants and lead clinicians found all aspects of the trial process, including randomisation, were acceptable and did not appear to cause distress. However, we await data from the main trial on the psychological impact of trial participation and acceptability of the MoleMate system.

This trial tests a novel service model of internal referral in general practice to Lead Clinicians who do not have dermatological training. We are conducting an economic evaluation of the use of the MoleMate system within this service model to establish its cost-utility compared with current best practice.

Our primary outcome measure is based on the clinical significance of a lesion, as determined by the actual management (biopsy or monitor) by a skin cancer specialist. This is a meaningful outcome in terms of health service delivery and the need to improve referral efficiency. While ideally we would have detection of melanoma as the primary outcome, this would require a much larger trial to have sufficient statistical power. We will capture data on melanoma incidence and mortality in all participants over 5 years. This will provide important data on the false negatives; lesions incorrectly diagnosed as benign.

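### The five-year melanoma incidence comparison appears to pool melanomas found through the index referral with those diagnosed later, so its hazard ratio has no defined favourable direction and can hide missed melanomas

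*Protocol article*

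**What the plan says.** Section 2.9.2 lists five-year melanoma incidence and mortality, taken from the regional cancer registry, as secondary clinical outcomes. Section 2.11 (Clinical outcomes) fixes the analysis: "From five-year Cancer Registry follow-up for all participants (incidence and mortality) survival analysis methods will be used". It names the log-rank test, Kaplan-Meier plots and Cox regression, and sets the population as "involving the full participant sample in each randomised group (referred plus non-referred) to assess overall effect of the introduction of the MoleMate system".

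The Discussion returns to these data. It says "We will capture data on melanoma incidence and mortality in all participants over 5 years", and then: "This will provide important data on the false negatives; lesions incorrectly diagnosed as benign".

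Two other statements bear on the point. Section 2.7.1 says "All lesions considered 'suspicious' by a Lead Clinician from both trial arms are referred to secondary care", through the two-week pathway, so melanomas found this way will be diagnosed near the start of follow-up. Section 2.11 also says "Histological diagnosis of melanoma will be summarised as a rate in each randomised group", with exact methods and all participants in the group as the denominator.

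The article nowhere separates registry melanomas diagnosed through the index referral from those diagnosed later. It sets no landmark time and does not say whether a higher or a lower incidence hazard is the better result.

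**The concern.** A registry records a melanoma however it came to light. In this trial the two routes mean opposite things. A melanoma diagnosed through the index referral is a success of the primary care decision. A melanoma diagnosed later in someone who was not referred may be a failure of it. Randomisation should balance the melanomas present at entry. Among these, the intervention mainly changes when each one is diagnosed. Better detection therefore raises early incidence and lowers later incidence, and a single ratio over five years adds the two.

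At stake is the use the Discussion makes of these data. Read on its own, an incidence hazard ratio near 1 would look reassuring about missed melanoma when it carries almost no information about it. A ratio below 1 could be credited to the arm that missed more.

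**Working it through.** The article gives no event count, hazard ratio or power for the five-year analysis, so there is no figure of its own to reproduce.

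**Inputs**
- Participants: 1150 randomised (section 2.10). Equal allocation is assumed, giving 1150 / 2 = 575 per arm.
- Melanomas present at entry, detection at the index visit, and the share of missed melanomas registered within five years: not in the document, so assumed below.
- New melanomas arising after entry: set to zero. An equal number added to each arm would pull the pooled ratio further towards 1.

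**Illustration 1: log-rank, in two blocks of time**

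Assume 17 melanomas per arm at entry (about 3% of 575), all registered within five years. Arm A finds 16 and misses 1. Arm B finds 11 and misses 6.

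- Early block: 16 + 11 = 27 events with 575 v 575 at risk. Expected in A = 27 × 575/1150 = 13.5.
- Late block: 1 + 6 = 7 events with 575 − 16 = 559 v 575 − 11 = 564 at risk. Expected in A = 7 × 559/1123 = 3.48.
- Total in A: observed 17, expected 13.5 + 3.48 = 16.98, so observed minus expected = 0.02.

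Total incidence is 17/575 in each arm and the hazard ratio is about 1.00. Later melanomas are 1/575 = 0.17% v 6/575 = 1.04%.

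**Illustration 2: hazard ratio under other assumptions**

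Let M be the melanomas per arm at entry, s the sensitivity of the index decision, and q the share of missed melanomas registered within five years. Index events are M·s and later events are M·(1 − s)·q. The hazard ratio, intervention over control, is taken as log(1 − events_int/575) / log(1 − events_ctrl/575).

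Take M = 12, with s = 0.90 in control and 0.70 in intervention. Index events are 10.8 (control) v 8.4 (intervention).

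| q | Later events, control v intervention | Total events, control v intervention | Pooled HR | Later-only HR |
|---|---|---|---|---|
| 1.0 | 1.2 v 3.6 | 12.0 v 12.0 | 1.00 | 3.0 |
| 0.8 | 0.96 v 2.88 | 11.76 v 11.28 | 0.96 | 3.0 |
| 0.5 | 0.6 v 1.8 | 11.4 v 10.2 | 0.89 | 3.0 |

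Here the intervention misses three times as many melanomas, yet its pooled hazard is equal or lower. With q = 1.0, the early ratio is 8.4/10.8 = 0.78 and the later ratio is 3.6/1.2 = 3.0. With the sensitivities swapped, the pooled ratio is 1.00, 1.04 and 1.12 for the same three values of q, while the later-only ratio is 0.33.

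The calculation was repeated with M = 6 and 18, and with sensitivities of 0.80 and 0.95 either way round. Over all scenarios the pooled ratio stayed between 0.89 and 1.12, while the later-only ratio ran from 0.25 to 4.0. Wherever the pooled ratio differed from 1, its power was about 3% to 5%. Power for later-only events was about 9% to 32%.

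**The case against.** The strongest reply is that the plan does not rest its case on this hazard ratio.

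- **Purpose.** A reader might infer that the Cox model is meant to measure false negatives. Section 2.11 gives its purpose as the overall effect of introducing the system. The false-negative sentence in the Discussion describes the data, not the hazard ratio. This stands. Even so, it is the only between-arm analysis fixed for the registry data, and as a measure of overall effect the incidence ratio still has no stated good direction.
- **The split is partly there.** The histological melanoma rate per randomised group comes close to a yield table, and later cases could be had roughly by subtraction. The Kaplan-Meier curves could also show an early gap that closes. This largely stands, but no later-melanoma endpoint is defined and none is compared with an interval.
- **Other checks.** A reader might infer that this is the only protection against missed melanoma. It is not. Expert review of non-referred lesions at three months, early recall, the six-month audit, and sensitivity and NPV all address missed lesions over a shorter term. The five-year mortality comparison is free of the pooling problem.
- **Proportional hazards.** It would be too strong to say that the assumption must fail. It fails in this way only if the arms differ in index detection. The log-rank test stays valid under the null, and Kaplan-Meier plots do not need the assumption.
- **Inference about events.** That index melanomas count as events is inferred from the stated population and the absence of any exclusion. The full protocol or SAP may define the event more narrowly.
- **Breslow thickness.** The sentence "Melanoma thickness (Breslow data) and other histological diagnoses will be summarised using the same approach" might be read as applying a test for rates to a measurement. The Background uses thickness categories (under 1 mm, over 4 mm), to which exact methods apply, so this is loose wording and not a demonstrated error.

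**Conclusion.** The point holds for incidence only. As described, the comparison appears to pool index-referral melanomas with later ones. If the arms differ in detection, the resulting hazard ratio sits near 1 or leans towards the arm that missed more. If every missed melanoma is registered within five years, the expected ratio is 1.00 whatever the difference in sensitivity. If some are not, it moves the wrong way, to 0.89 or 1.12 at the extremes examined.

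This rests on equal numbers of melanomas at entry in the two arms, on index cases counting as events, and on assumed melanoma counts, sensitivities and registration shares. The cancellation does not depend on the count: 6, 12 or 18 per arm gives the same hazard ratios to within 0.01. The documents do not support reading this as a failure of the trial's whole safety assessment. It is a secondary outcome whose planned comparison cannot by itself carry what the Discussion expects of the data.

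**What to change.** Keep all randomised participants as the denominator and split registry melanoma incidence in two.

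- (a) Melanomas diagnosed through the index referral, reported by arm as yield.
- (b) Melanomas diagnosed later and not through the index referral, compared between arms as a proportion of those randomised, with an exact 95% confidence interval for the difference. Name this as the false-negative measure and state that lower is favourable. Cases that surface through the three-month review or the six-month audit belong here, since the index decision was not to refer. Where possible, match by site to the study lesion, so that new melanomas elsewhere can be told apart.

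Keep total incidence, with its Kaplan-Meier plot, as descriptive, and keep the mortality analysis as planned. Do not drop referred participants from the comparison: referral is decided after randomisation, so the arms would no longer be comparable.

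The cost is a few lines of analysis-plan wording and linkage of registry entries to the trial's referral records, which the Discussion says can be tracked. Events in (b) will be few and the intervals wide, and the report should say so.

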##### 3. Clinician outcomes

Continuous outcomes at the level of clinician such as confidence and attitudes, and change in these, towards the MoleMate system will be summarised using a mean score and 95% confidence interval and reporting the proportion of clinicians above a threshold of adequate confidence.

Assessment for learning effects will be undertaken using randomised comparisons of differences in proportions across 'naive' and 'potentially contaminated' periods: if there is an improvement in performance in the comparison arm and the intervention effect size becomes smaller through Lead Clinicians' sequence of lesions assessed, and this is a systematic effect established across the study clinicians, this would be evidence of either a learning effect or more general contamination.

The diagnostic performance of the seven-point checklist and the Index of Suspicion scale will be assessed and compared between the intervention and comparison groups.

##### 4. Patient outcomes

Continuous secondary outcomes at the participant level, such as anxiety, cancer worry, and satisfaction with the consultation will be compared using a t-test, assuming no clustering effects are identified. Analyses will be unadjusted cross-sectional comparisons between groups. Change over time will also be summarised, reporting means at baseline and mean changes between time-points.

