### 2.6 Study procedures

At the trial consultation, the Lead Clinician consents and randomises the patient into the 'comparison' or 'intervention' group.

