**Psychological measures (questionnaire)**						
Anxiety: short form STAI^†^			√	√		
Cancer worry: modified cancer worry scale			√	√		
Satisfaction with LC consultation^¥^			√			

^† ^Spielberger State-Trait Anxiety Inventory

^¥ ^Items from Europep instrument relating to the dimensions of care

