##### Patient outcomes

Participants will complete the following psychological measures within 1 week and at 3 months after their consultation with the Lead Clinician:

- General and cancer-specific worry: Anxiety using the Spielberger State-Trait Anxiety Inventory, STAI [24] and a modified cancer worry scale [25];

- Satisfaction with the trial consultation using dimensions of care items from Europep [26].

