### 2.10 Sample size

Our pilot study confirmed projected recruitment rates (6-8 participants per practice per month) and referral rates (approximately 2 referrals per practice per month). Based on these, to detect an increased biopsy rate of 10% amongst those referred of 22% ('intervention' group) versus 12% ('comparison' group), an odds ratio of 2.0, with 80% power at the 5% significance level, would require 442 analysed in the primary outcome sample of referred lesions. With the involvement of 15 practices, this would require 30 referred lesions per practice. Assuming a 25% referral rate this could be achieved by randomising 120 patients per practice (1800 total) with an assumed recruitment rate of 90 per year over a 16-month period.

A blinded interim analysis, presented at the Trial Steering Committee meeting half-way through the study (September 2009) after 747 participants had been randomised, established a lesion referral rate of 28% (254/913), a mean cluster size amongst the referred sample of 1.06 (254 lesions from 239 participants), and that 55% of the referred lesions were assessed by the dermatology experts to be 'clinically significant' in the combined arm data. In this context of a higher rate of biopsy or monitoring, the clinically worthwhile difference was altered to a 15% difference (an odds ratio of 1.8) from 45% to 60%. A target total of 400 referred lesions from approximately 380 patients would provide 80% power to detect this difference at the 5% level of significance, and would require an estimated 1450 study lesions from 1150 randomised participants.

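### Anxiety and cancer worry are measured twice but compared by separate unadjusted t-tests; a joint model of both time points would use the 1-week scores in the 3-month comparison, for a modest gain in precision and some protection against dropout

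*Protocol article*

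**What the plan says.** Section 2.9.2 (Patient outcomes) has anxiety and cancer worry completed "within 1 week and at 3 months after their consultation with the Lead Clinician". Table 1 ticks both measures at both times; satisfaction is ticked once, so it is left aside here.

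Section 2.11 (4. Patient outcomes) says these outcomes "will be compared using a t-test, assuming no clustering effects are identified", and then: "Analyses will be unadjusted cross-sectional comparisons between groups". The only joint use of the two time points is descriptive: "Change over time will also be summarised, reporting means at baseline and mean changes between time-points".

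Randomisation comes before both questionnaires. Section 2.6 states: "At the trial consultation, the Lead Clinician consents and randomises the patient into the 'comparison' or 'intervention' group". The 1-week score is therefore a post-randomisation outcome, and Table 1 shows no questionnaire before randomisation.

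**The concern.** The same scale is completed twice by the same person, so the 1-week score carries information about a missing 3-month score. A cross-sectional test at 3 months has no place for it. A participant who returns the first questionnaire but not the second counts in the 1-week comparison and adds nothing to the 3-month one.

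Two things could follow. The first is a loss of precision, which needs only some missing 3-month questionnaires and a correlation between the scores. The second is bias, if the participants who stop replying differ in 1-week worry in one way in one arm and another way in the other. The design leaves room for that. No blinding of participants is described, the scan is visible to them, and referred and non-referred participants follow different pathways before 3 months. The section on secondary outcomes also allows that referral volume may differ by arm. The Discussion says that the evidence on psychological impact awaits the main trial, and these comparisons will supply it.

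**Working it through.** **What the documents supply.** Two measurement times (2.9.2, Table 1); t-test, unadjusted, cross-sectional (2.11); and, for scale, the revised target, which "would require an estimated 1450 study lesions from 1150 randomised participants" (2.10). With 1:1 allocation assumed, that is 1150 / 2 = 575 per arm. The article gives no sample size, SD, correlation or response rate for anxiety or cancer worry, so there is no stated figure to reproduce.

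**Assumptions (none from the documents).** 85% return the 1-week questionnaire, so n1 = 0.85 x 575 = 489 per arm. A share p of these, 0.6 to 0.8, also reply at 3 months, so n2 = p x n1. The correlation r between the two scores is 0.6 to 0.75. Scores are in SD units.

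**Precision.** The variance of the 3-month difference is 2/n2 for the t-test and 2[(1 - r²)/n2 + r²/n1] for a model of both scores. The ratio of standard errors (SE) is therefore sqrt(1 - (1 - p)r²).

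| p | r | SE ratio | SE smaller by | Equivalent extra responders |
|---|---|---|---|---|
| 0.8 | 0.6 | sqrt(1 - 0.2 x 0.36) = 0.963 | 3.7% | 1/0.928 - 1 = 8% |
| 0.7 | 0.6 | sqrt(1 - 0.3 x 0.36) = 0.944 | 5.6% | 1/0.892 - 1 = 12% |
| 0.6 | 0.6 | sqrt(1 - 0.4 x 0.36) = 0.925 | 7.5% | 1/0.856 - 1 = 17% |
| 0.7 | 0.75 | sqrt(1 - 0.3 x 0.5625) = 0.912 | 8.8% | 1/0.831 - 1 = 20% |

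The extreme corner, p = 0.6 with r = 0.75, would give 1 - sqrt(1 - 0.4 x 0.5625) = 12%. A simulation of 2000 runs per setting agrees with the first three rows (0.0706 v 0.0678, 0.0760 v 0.0715, 0.0829 v 0.0770). For the last row it gave 0.0750 v 0.0678, about 10%, slightly above the formula.

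**Bias.** Suppose the log-odds of replying at 3 months change by b per SD of 1-week score. The mean 1-week score among responders then shifts by about b(1 - p), and the mean 3-month score by about r x b x (1 - p). With equal response rates, the arm difference is off by r(1 - p) times the difference in b between arms.

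- Slopes -0.2 v -0.6, p = 0.7, r = 0.6: 0.6 x 0.3 x 0.4 = 0.072 SD (simulated size 0.069).
- Slopes -0.3 v 0, same p and r: 0.6 x 0.3 x 0.3 = 0.054 SD (simulated size 0.055).

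The t-test SE at p = 0.7 is sqrt(2/(0.7 x 489)) = 0.076, so these biases are about 0.9 and 0.7 of a standard error. With the same slope and response rate in both arms the formula gives zero. A separate large-sample simulation (1,000,000 per arm, 10-30% dropout, r = 0.5 to 0.7) found at most 0.002 SD in that case. With a 0.3 SD arm effect at 1 week only (equal slopes, 20% dropout, r = 0.6) it found about 0.004 SD.

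Steeper contrasts in that simulation (slopes 0 v 0.7, or +0.5 v -0.5) gave 0.03 to 0.20 SD. Those slopes were chosen to show the mechanism and nothing in the article supports them. The joint estimate stayed within 0.003 SD of zero throughout, but by construction: missingness was made to depend on the 1-week score alone.

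**The case against.** The strongest reply is that the article never says the t-test is confined to responders. It does not mention non-response, complete cases or imputation, and handling of missing questionnaires is commonly left to the analysis plan. An unadjusted comparison at each time is compatible with multiple imputation that uses the 1-week score. A reader might infer that the article fixes a responder-only analysis; it does not. The point therefore holds only if no imputation is added elsewhere.

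Second, the stated comparison is valid under randomisation, and with complete data the joint model returns the same mean differences. That is correct, and it makes this an improvement and not an error.

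Third, a reader might infer that the 3-month result will be biased. Nothing in the article shows that reply depends on worry, still less that it does so differently by arm. Knowing that one was scanned does not establish it.

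Fourth, a reader might infer that the joint model removes whatever bias there is, or that its assumption is the milder one. Neither follows. If reply depends on unobserved 3-month worry, bias can remain. The t-test tolerates such dependence when it is the same in both arms, so the two conditions are not nested.

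Finally, the 1-week scores are not thrown away: they count in the 1-week comparison and are absent only from the 3-month contrast.

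What survives is that the method is a stated choice. The only condition attached to the t-test concerns clustering, and mean changes need both scores, so they do not help a participant who has only one.

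**Conclusion.** The concern holds as an optional improvement to secondary patient outcomes; the primary comparison of referral PPV is untouched. Unless an unshown plan adds imputation, the 3-month comparison of anxiety and cancer worry leaves out usable 1-week information. Under the assumed response and correlation in the four settings worked, the cost is a standard error for which a joint model would give a value about 4-9% smaller. This needs no arm-specific dropout.

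The bias is hypothetical: about 0.05-0.07 SD under assumed slopes, only if 3-month response relates to the 1-week score differently by arm, and negligible otherwise. The documents do not support a claim that such bias is present, and its size cannot be known from them.

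**What to change.** For each of anxiety and cancer worry, replace the separate t-tests as the main analysis with one linear mixed model for the 1-week and 3-month scores. It should have terms for arm, time and arm-by-time and an unstructured within-participant covariance. Report the arm difference with its 95% confidence interval at each time from that model, and keep the t-tests as a simple check. The 1-week score should enter as an outcome, not as a baseline covariate, because it is taken after randomisation. For the same reason the mention of baseline means in 2.11 should be reworded as 1-week means.

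The cost is a change of analysis wording and a standard model, with no new data. The downside is reliance on missingness at random given the 1-week score. The model does not correct dropout driven by unobserved 3-month worry, and it does not help participants who return neither questionnaire. Reporting response at each time by arm, and 3-month response by 1-week score within arm, would show whether the bias question arises at all.
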